### Sample size

The sample size will be estimated using PASS 15.0 software. Knee extensor peak torque will be selected as the primary outcome for sample size calculation. Based on relevant preliminary and published experimental data, the expected mean and standard deviation of post-intervention knee extensor peak torque in the three groups will be used to estimate an effect size of Cohen’s *f* = 0.55. With a two-sided alpha level of 0.05, statistical power of 0.90, and one-way analysis of variance for three-group comparison, the minimum required sample size is 16 participants per group. Allowing for an anticipated dropout rate of approximately 15%, 19 participants will be enrolled in each group, yielding a total sample size of 57 participants (32).

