### Statistical analysis

Two analysis sets will be used. The intention-to-treat set will include all randomized participants in their originally allocated groups regardless of adherence or withdrawal. The per-protocol set will include participants who complete the full intervention protocol without major protocol deviations. The primary analysis will be based on the intention-to-treat principle, and the per-protocol analysis will be used as a sensitivity analysis.

Missing data will be handled using multiple imputation when the missingness mechanism is considered missing at random. Baseline knee muscle strength, dynamic balance index values, age, height, and weight will be considered predictor variables for imputation. Five imputed datasets will be generated using a multiple linear regression model in SPSS 25.0. Pooled estimates will be calculated according to Rubin’s rules. If missing data are minimal, complete-case analysis may be reported as a supplementary analysis.

Categorical variables will be expressed as n (%). Normally distributed quantitative variables will be presented as mean ± standard deviation, and non-normal data as median (interquartile range). Normality will be tested with the Shapiro–Wilk test, and variance homogeneity with Levene’s test. For within-group pre–post comparisons, paired t-tests will be used for normally distributed data; otherwise, Wilcoxon signed-rank tests will be applied. Between-group differences will be assessed using one-way ANOVA for parametric data, followed by Bonferroni-adjusted pairwise comparisons when the overall effect is significant. Non-parametric data will be analyzed with the Kruskal–Wallis test, followed by Dunn–Bonferroni pairwise comparisons. Categorical variables will be compared using the chi-square test or Fisher’s exact test. Given three primary outcomes (knee extensor peak torque, knee flexor peak torque, and hamstring-to-quadriceps ratio), a Bonferroni correction will be applied to control multiplicity, with a significance threshold set at *p* < 0.017 (0.05/3). Secondary outcomes are exploratory, a two-sided *p* < 0.05 will be used without multiplicity correction.

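### Five imputations leave avoidable Monte Carlo noise in the primary verdicts: modest at the planned 15% dropout, larger if loss is heavier, and removable almost free of charge

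*Protocol article*

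**What the plan says.** All the relevant text is in the protocol article.

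- **Number of imputations** (Statistical analysis): "Five imputed datasets will be generated using a multiple linear regression model in SPSS 25.0".
- **Pooling** (Statistical analysis): "Pooled estimates will be calculated according to Rubin’s rules".
- **Role of the imputed data** (Statistical analysis): "The primary analysis will be based on the intention-to-treat principle, and the per-protocol analysis will be used as a sensitivity analysis". The intention-to-treat set holds all 57 randomized students. Missing values are multiply imputed when judged missing at random, so the imputations feed the primary result directly.
- **Test** (Statistical analysis): "Between-group differences will be assessed using one-way ANOVA for parametric data, followed by Bonferroni-adjusted pairwise comparisons when the overall effect is significant".
- **Decision threshold** (Statistical analysis): for the three primary outcomes, "a Bonferroni correction will be applied to control multiplicity, with a significance threshold set at" p < 0.017, that is 0.05/3.
- **Expected loss** (Sample size): "Allowing for an anticipated dropout rate of approximately 15" per cent, with 19 enrolled per group.

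The article does not tie the number of imputations to the amount of missing data.

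**The concern.** With m = 5 imputed datasets, the between-imputation variance is estimated from five values, on 4 degrees of freedom. The pooled estimate, its standard error and the p-value then vary from one set of random draws to the next. When the p-value falls near a fixed cut-off, that variation alone can decide whether a primary outcome is declared significant.

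What is at stake is reproducibility. Someone repeating the planned analysis on the same 57 records could reach a different verdict on a primary outcome, for a reason unrelated to the students or the interventions. The stated number can be changed before any data are analysed.

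**Working it through.** **1. The plan's own figures.** For a one-way ANOVA with three groups, noncentrality is N·f². With f = 0.55 and alpha 0.05, power is 0.900 at 15 per group and 0.920 at 16, so the stated 16 per group does reach 0.90. Inflating for dropout, 16/(1 − 0.15) = 18.8, giving 19 per group and 57 in total, as stated. Expected missing post-tests: 0.15 × 57 = 8.55, about 9.

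**2. Inputs to the check.**
- From the article: 57 randomized, 19 per arm as planned; f = 0.55; about 15% loss; m = 5; Rubin's rules; threshold 0.05/3 = 0.0167.
- Assumed, because the article does not give them: baseline-to-post correlation 0.7 (range 0 to 0.85); equally spaced group means; post-tests missing completely at random; group included in the imputation model; the ANOVA pooled by the multivariate Rubin (D1) test; heavier loss of 30% or 37%.

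**3. Method.** For each imputation, take the two group-mean contrasts Q and their covariance U. With k = 2, average them to Q̄ and Ū, let B be the between-imputation covariance, and compute

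r = (1 + 1/m)·tr(B Ū⁻¹)/k, D1 = Q̄ᵀŪ⁻¹Q̄ / [k(1 + r)],

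referred to an F distribution. Each simulated trial was imputed twice, independently, by Bayesian linear regression. The flip rate is the share of trials in which the two verdicts at 0.0167 differ. There were 2,500 to 4,000 trials per setting. The standard error is about 0.3 to 0.4 points for a rate of 5% (for example √(0.05 × 0.95/2500) = 0.44 points).

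**4. Central case** (f = 0.55, correlation 0.7, five predictors plus group), flip rate for the overall ANOVA:

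| Loss | m = 5 | m = 20 | m = 50 | m = 100 |
|---|---|---|---|---|
| 15% (9 of 57) | 4.4-5.4% | 2.2-2.4% | 1.3-1.5% | 1.0% |
| 30% (17 of 57) | 12.4-12.7% | 4.8-5.4% | 2.9-3.7% | 2.3% |

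With one predictor plus group, the m = 5 figures are 4.6% at 15% loss and 10.6% at 30%; with m = 50 they are 1.5% and 2.8%.

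Further runs with equal loss in every arm agree. With 3 of 19 missing, flips were 3.7-4.5% (m = 5) against 1.0-1.5% (m = 50). With 7 of 19 missing (37%), they were 12.6-13.2% against 2.9-3.4%.

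**5. Sensitivity at m = 5.**

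| Setting | 15% loss | 30% loss |
|---|---|---|
| f = 0.55, correlation 0 | 8.9% | 19.7% |
| f = 0.55, correlation 0.5 | 8.2% | 15.9% |
| f = 0.55, correlation 0.85 | 2.5% | 7.2% |
| f = 0.40, correlation 0.7 | 7.4% | 14.0% |
| No effect, correlation 0.7 | 0.9% | 1.1% |

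**6. Pairwise verdict.** For the combined arm against Tai Chi Chuan alone, judged at 0.0167/3 in the central case, flips are about 7% at 15% loss and 16-18% at 30%. With m = 50 they are about 1.5% and 3-4%.

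**7. Validity and power.** With 3 of 19 missing per arm:
- Rejection under no effect was 1.8% for both m = 5 and m = 50 (3,000 trials), in line with the nominal 1.67%.
- Power was 84.7% against 85.6%.
- With a fraction of missing information of about 0.10, the relative efficiency of m = 5 is 1/(1 + 0.10/5) = 98%.

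With 7 of 19 missing, m = 5 does cost power: 74.5% against 78.7% in one set of runs, and about 71% against 79% in another.

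**The case against.** **Rubin's rules already allow for a finite number of imputations.** This stands. At the planned loss the m = 5 test holds its level and gives up about one point of power. A reader might infer that the primary test is invalid or its error rate inflated. The calculations show neither; what remains is run-to-run noise.

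**The figure near 13% does not describe the planned trial.** This also stands. It needs 30-37% loss, while the article anticipates about 15%. The withdrawal rule in Table 1 (two consecutive or three cumulative missed sessions) could raise loss. However, withdrawn students stay in the intention-to-treat set, and the article does not say that they will miss the post-test.

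**The rates rest on assumptions.** True, which is why ranges are given. One assumption also departs from the text. The listed predictors are: "Baseline knee muscle strength, dynamic balance index values, age, height, and weight will be considered predictor variables for imputation". Group is not among them. Leaving it out raises the flip rate at 15% loss to 12.7%, but that is a consequence of the imputation model and should not be charged to the choice of five.

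**The seed.** A reader might treat the unstated seed as a defect, or suspect that one could be chosen to suit. A seed is detail that a condensed article leaves to the analysis plan or the code, and the Blinding section keeps the analysts blind to group until the main analysis is done. Neither reading is supported.

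**Fifty is partly a matter of preference.** Fair: in the central case 20 imputations achieve roughly 70-80% of the reduction that 50 does, and some flips remain at any number. That does not argue for keeping five.

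**Conclusion.** The point holds as a free improvement. At the planned 15% loss and planned effect, about 4-5% of trials would change their overall verdict on a primary outcome when the imputation is rerun (2.5-9% over correlations 0 to 0.85), against about 1-1.5% with 50 imputations. At 30-37% loss, which the article does not anticipate, the rate is about 11-13% (7-20% over the same correlations at 30% loss), against about 3-4%. Only at the heaviest of these losses, 37%, is there a clear power cost, of about 4 to 8 points. If there is no true effect, flips are about 1%.

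The sizes depend on the assumed correlation, on group being in the imputation model and on D1 pooling. The direction does not: in every setting where both were run, 50 imputations cut the flip rate by about two-thirds or more compared with five.

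**What to change.** In the Statistical analysis section, replace five with at least 50 imputed datasets. If a smaller number is preferred, 20 already secures most of the gain. Fix the random seed in the analysis code in advance as routine practice, since a larger number reduces flips without abolishing them.

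The cost is one number in the text and seconds of computing. Sample size, data collection and the tests are unaffected. Under the Protocol amendments section, an important change to analysis methods goes to the ethics committee before implementation, so the edit can travel with any other amendment.

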## Objectives and hypotheses

The primary objective is to evaluate the effects of an 8-week Tai Chi Chuan combined with unstable resistance training programme on knee flexor and extensor strength in female college students, compared with Tai Chi Chuan alone and unstable resistance training alone.

The secondary objective is to compare the effects of the three intervention modalities on dynamic balance capacity under eyes-open and eyes-closed conditions.

The main hypothesis is that the combined intervention will produce greater improvements in knee flexor peak torque, knee extensor peak torque, H/Q ratio, and dynamic balance indices than either single-modality intervention. A secondary hypothesis is that Tai Chi Chuan alone will show particular advantages in proprioception-dependent balance and H/Q optimization, while unstable resistance training alone will show particular advantages in rapid improvement of extensor strength.

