### Outcome measures

All outcome assessments will be completed within 1 week before the intervention and within 1 week after completion of the 8-week intervention. The testing sequence will remain consistent across participants and time points. The dominant leg (preferred kicking leg) will be used for knee muscle strength testing (Table 5).

**Table 5 tab5:** Outcome measures, assessment tools and interpretation criteria.

Outcome category	Measure	Instrument	Interpretation
Primary outcome	Knee extensor peak torque (EPT)	Multi-joint isokinetic strength testing and training system, Model A8-2, at 60 degrees/s	Higher value indicates greater knee extensor strength.
Primary outcome	Knee flexor peak torque (FPT)	Multi-joint isokinetic strength testing and training system, Model A8-2, at 60 degrees/s	Higher value indicates greater knee flexor strength.
Primary outcome	Hamstring-to-quadriceps ratio (H/Q)	Calculated from flexor and extensor peak torque	Higher balanced ratio indicates improved flexor-extensor strength balance.
Secondary outcome	Overall Stability Index (SI)	Biodex Balance System, bipedal dynamic balance test	Lower value indicates better balance capacity.
Secondary outcome	Anteroposterior Stability Index (APSI)	Biodex Balance System, bipedal dynamic balance test	Lower value indicates better anterior–posterior stability.
Secondary outcome	Mediolateral Stability Index (MLSI)	Biodex Balance System, bipedal dynamic balance test	Lower value indicates better medial-lateral stability.
Safety outcome	Adverse events and exercise-related discomfort	Instructor record form and participant report	Events summarized by type, severity, relation to intervention, and outcome.

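### The between-group tests leave out the baseline value and a normality test picks the method: valid on average, but less precise than the collected data allow

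*Protocol article*

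**What the plan says.** All outcomes are measured twice (Outcome measures): "All outcome assessments will be completed within 1 week before the intervention and within 1 week after completion of the 8-week intervention". The main hypothesis (Objectives and hypotheses) concerns change: the combined programme "will produce greater improvements in knee flexor peak torque, knee extensor peak torque, H/Q ratio, and dynamic balance indices" than either single modality. The trial is sized on the later value alone (Sample size): "the expected mean and standard deviation of post-intervention knee extensor peak torque in the three groups will be used".

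The between-group method is in Statistical analysis: "Between-group differences will be assessed using one-way ANOVA for parametric data". The alternative follows: "Non-parametric data will be analyzed with the Kruskal–Wallis test, followed by Dunn–Bonferroni pairwise comparisons". The checks that precede them are: "Normality will be tested with the Shapiro–Wilk test, and variance homogeneity with Levene’s test".

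No ANCOVA, mixed model or baseline covariate is named. Baseline outcome values are used in the within-group paired tests and in the imputation model: "Baseline knee muscle strength, dynamic balance index values, age, height, and weight will be considered predictor variables for imputation". Allocation is by simple randomisation (Randomization and allocation concealment). Five imputed datasets are planned, and the three primary outcomes are tested at 0.017.

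**The concern.** A one-way ANOVA has group as its only factor. The plan therefore collects a baseline measurement of every outcome and then leaves it out of the comparison between arms. Three things follow.

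- **Precision.** The part of the between-person variation that baseline could explain stays in the error term.
- **Chance imbalance.** Simple randomisation with about 19 women per arm does not balance baseline strength. Whatever difference the allocation happens to produce stays in the observed contrast.
- **A primary analysis that is not fully fixed.** The article does not say whether week-8 values or changes are compared. The hypothesis points to change and the sample size to week-8 values. The choice between means and ranks is left to a normality test on the trial data, outcome by outcome.

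At stake are power and the credibility of the estimated differences between the combined arm and each single-modality arm.

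**Working it through.** **Inputs from the article:** three groups, f = 0.55 on post-intervention extensor torque, sizing alpha 0.05, power 0.90, 16 per group, 15% dropout, 19 enrolled per group (Sample size); testing threshold 0.05/3 (Statistical analysis). **Assumed:** the within-group baseline–post correlation r, which the article does not give, taken as 0.3 to 0.8, and equal SDs at the two time points.

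**1. The plan's own figure.** For a one-way ANOVA, power comes from the noncentral F with λ = N·f² and df 2 and N − 3. With 16 per group, N = 48 and λ = 48 × 0.3025 = 14.52, so power at alpha 0.05 is 0.920. Fifteen per group already gives 0.9001, so the stated 16 is sufficient. Then 16/0.85 = 18.8, rounded up to 19, and 3 × 19 = 57. The figure reproduces to within one participant per group. At 0.05/3 the same ANOVA has power 0.825 with 16 per group and 0.900 with 19.

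**2. Variance.** Relative to an ANOVA of week-8 values, ANCOVA has variance 1 − r² and a change-score ANOVA has 2(1 − r). The ratio of ANCOVA to change score is therefore (1 + r)/2.

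| r (assumed) | ANCOVA / week-8 ANOVA | ANCOVA / change-score ANOVA |
|---|---|---|
| 0.3 | 0.91 | 0.65 |
| 0.5 | 0.75 | 0.75 |
| 0.7 | 0.51 | 0.85 |
| 0.8 | 0.36 | 0.90 |

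**3. Power with 16 per group and f = 0.55 on week-8 values.** ANCOVA uses λ = N·f²/(1 − r²), with df 2 and N − 4. This ignores the small loss from estimating the slope when baselines differ by chance.

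| Analysis | alpha 0.05 | alpha 0.05/3 |
|---|---|---|
| Week-8 ANOVA | 0.920 | 0.825 |
| ANCOVA, r = 0.3 | 0.942 | 0.865 |
| ANCOVA, r = 0.5 | 0.975 | 0.930 |
| ANCOVA, r = 0.7 | 0.998 | 0.991 |
| ANCOVA, r = 0.8 | >0.999 | >0.999 |

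If changes were analysed instead (λ = N·f²/[2(1 − r)]), power at 0.05/3 would be 0.650, 0.825, 0.976 and 0.999 for the same four values of r.

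**4. Chance imbalance.** With exactly 19 per arm, the baseline difference between two arms has SD √(2/19) = 0.324 in baseline SD units. For a given pair, P(|difference| > 0.3) = 2[1 − Φ(0.3/0.324)] = 0.355. By simulation, at least one of the three pairs exceeds 0.3 SD with probability 0.62. For 0.5 SD the figures are 0.12 and 0.27.

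Given a baseline difference d, an ANOVA of week-8 values carries r·d into the contrast and a change-score ANOVA carries (r − 1)·d; ANCOVA carries about none. With d = 0.5 and r = 0.7 these are 0.35 SD and −0.15 SD.

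**5. The normality switch.** Suppose Shapiro–Wilk is run in each arm at 0.05, which the article does not specify. With truly normal data, at least one of three arms then fails with probability 1 − 0.95³ = 0.143 per outcome; simulation with 16 per arm gives 0.142. The result can also differ across the five imputed datasets, so that some would go to ANOVA and others to Kruskal–Wallis.

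**The case against.** The strongest reply is that nothing here is invalid. Under randomisation, an unadjusted ANOVA of week-8 values or of changes is unbiased on average and keeps its type I error. That stands. A reader might infer that the planned comparison is biased; the documents do not support this. Imbalance matters only conditionally on the allocation obtained, and otherwise the loss is one of precision.

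A reader might also infer that leaving out baseline is what makes the trial underpowered. It is not. The figure of 0.825 arises because the trial is sized at alpha 0.05 and tested at 0.017, which is a separate point. At the sizing alpha the stated ANOVA has 0.920, and with all 57 women observed it has about 0.900 even at 0.05/3.

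The gain depends on an unstated correlation and is modest at r = 0.3. The power gains in the second table also apply only if week-8 values are analysed. If changes are analysed, baseline already enters by subtraction, and for r of 0.7 to 0.8 ANCOVA saves only 10% to 15% of the variance. Both objections limit the size of the point. They do not remove it, because ANCOVA has the lower variance at every r in the table on either reading.

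It is tempting to add that Levene's test has no consequence. The text is unclear there: Levene may be part of how data are classed as parametric, so no weight is put on it.

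An unseen analysis plan does not answer the point. The article states the method, and a plan naming ANCOVA would contradict that text.

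**Conclusion.** The point holds as a should-fix. The stated between-group tests are valid on average but discard information already collected. Over assumed r from 0.3 to 0.8, ANCOVA would cut the variance by 9% to 64% against an analysis of week-8 values, and by 35% to 10% against change scores. With about 19 per arm and simple randomisation, a baseline gap above 0.3 SD in at least one pair of arms is more likely than not (about 0.62, assuming exactly 19 per arm).

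The choice between week-8 values and changes is left open, and the choice between means and ranks is left to the data. The size of the gain rests on the assumed r and on equal SDs at the two time points. The existence of a gain over either ANOVA does not depend on a particular r within the range shown.

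**What to change.** For each primary outcome, prespecify an ANCOVA of the week-8 value on group, with that outcome's own baseline value as covariate. Report adjusted mean differences with confidence intervals for T + URT versus TCC and T + URT versus URT. Use the same model for the secondary outcomes for consistency; they are declared exploratory, so this part is less pressing.

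Remove the normality-test switch and check the model residuals instead. Keep a rank-based analysis, or one with small-sample-corrected robust standard errors such as HC3, only as a labelled sensitivity analysis. Uncorrected robust standard errors are risky with 16 to 19 per arm.

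The cost is wording and one degree of freedom per model, with no new data. Because it alters analysis methods, the change goes through the ethics review described under Protocol amendments. It should be made before group codes are released.

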**Discussion:**

This trial is designed to determine whether Tai Chi Chuan combined with unstable resistance training provides superior improvements in knee muscle function and dynamic balance compared with either intervention alone.

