To our knowledge, no three-arm RCT has directly compared Tai Chi Chuan combined with unstable resistance training versus each intervention alone in sedentary female college students, despite prior work examining Tai Chi with instability, vibration, or core training in other populations or designs (18, 42). Existing Tai Chi studies have largely focused on older adults or clinical populations, with limited data on muscle strength gains in young females (12, 43). Unstable resistance training studies have mainly involved healthy or athletic populations, rarely examining the hamstring-to-quadriceps ratio or eyes-closed dynamic balance (39, 44, 45). This protocol fills this gap by evaluating a central-peripheral complementary approach. Conversely, if no added benefit is found, this would suggest excessive neuromuscular demand without further gain — an equally informative finding. By comparing three arms, this trial will provide the first high-level evidence on whether combining these two training philosophies yields synergistic effects on knee function and dynamic balance in young sedentary women.

This protocol includes several methodological strengths. First, the randomized three-arm design allows direct comparison between two single-modality interventions and their combination. Second, objective laboratory measures will be used for both strength and balance outcomes. Third, blinded outcome assessment and statistical analysis will reduce bias. Fourth, both intention-to-treat and per-protocol analyses will be planned to evaluate robustness. Fifth, intervention progression, heart rate monitoring, and standardized warm-up and cool-down procedures will improve intervention fidelity and safety.

The study also has limitations. The trial will be conducted at a single center and will include only healthy female college students aged 18–22 years, which may limit generalizability to male students, older adults, patients, or athletes. The intervention period will last 8 weeks, and long-term follow-up is not planned in the current protocol; therefore, persistence of training effects will remain uncertain. The study focuses on knee muscle strength and dynamic balance rather than actual injury incidence. In addition, future studies may incorporate advanced evaluation frameworks such as feature fusion and machine learning into outcome assessments to improve the precision of functional ability measurements (46).

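### The main hypothesis rests on two contrasts that the sample size does not power, and the likely pairwise threshold of about 0.0056 lowers their power further without need

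*Protocol article*

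**What the plan says.** Objectives and hypotheses: the combined programme is expected to improve knee strength, the H/Q ratio and balance more "than either single-modality intervention". The abstract's Discussion gives the trial's purpose as finding out whether the combination "provides superior improvements in knee muscle function and dynamic balance compared with either intervention alone".

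Sample size: extensor peak torque is used "to estimate an effect size of Cohen’s *f* = 0.55". The calculation is described as "With a two-sided alpha level of 0.05, statistical power of 0.90, and one-way analysis of variance for three-group comparison", so that "the minimum required sample size is 16 participants per group". After about 15% dropout, 19 per group are enrolled.

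Statistical analysis: groups are compared by one-way ANOVA, "followed by Bonferroni-adjusted pairwise comparisons when the overall effect is significant", or by Kruskal–Wallis with Dunn–Bonferroni pairs. A separate sentence sets p < 0.017 (0.05/3) because there are three primary outcomes. No threshold for a single pair is given.

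Discussion: "if no added benefit is found, this would suggest excessive neuromuscular demand without further gain".

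**The concern.** The claim the trial is meant to support needs T + URT vs TCC and T + URT vs URT to succeed together. The omnibus F can be significant because TCC and URT differ, or because T + URT beats only one of them, yet it is the only test with stated power. The decisive tests also appear to be corrected twice, once for outcomes and once for pairs.

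If so, the real power for the main claim is far below the stated 90%. A true benefit would then often go unproven, and the Discussion would read that result as a mechanism.

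**Working it through.** **1. The plan's own figure.** Inputs from Sample size: f = 0.55, alpha 0.05, power 0.90, three groups. Power comes from the noncentral F with df 2 and N − 3 and λ = N·f². At 16 per group, λ = 48 × 0.3025 = 14.52 and power is 92.0%; 15 per group already gives 90.0%. Dropout: 16/0.85 = 18.8, so 19. The stated figures reproduce.

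**2. Omnibus test at the planned level.** At 0.05/3 = 0.0167, omnibus power is 82.5% with 16 per arm and 90.0% with 19.

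**3. Pairwise threshold.** A Bonferroni-adjusted p (raw p × 3) compared with 0.0167 means raw p < 0.0167/3 = 0.0056.

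**4. Patterns of means (assumed; the protocol gives none).** f is the SD of the three means divided by the within-group SD.
- Single arms equal, means (0, 0, d): f = d√2/3, so d = 0.55 × 3/√2 = 1.167 SD for both contrasts.
- Equally spaced, step s: f = s√(2/3), so s = 0.674 SD. The contrasts are 0.674 and 1.347 SD.

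**5. Power to beat both arms.** Simulation with 200,000 trials per case: normal data, equal variances, pooled-variance t tests. Success requires a significant ANOVA and both contrasts significant in favour of T + URT. The ANOVA gate is 0.0167 in the last two columns and 0.05 in the column without correction.

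| Per arm | Pattern | Omnibus at 0.05 | Both, no correction (0.05) | Both, pairs at 0.0167 | Both, pairs at 0.0056 |
|---|---|---|---|---|---|
| 16 | single arms equal | 92.0% | 82.6% | 67.3% | 50.5% |
| 16 | equally spaced | 92.0% | 45.8% | 28.8% | 16.8% |
| 19 | single arms equal | 96.0% | 89.6% | 78.0% | 63.4% |
| 19 | equally spaced | 96.0% | 52.9% | 35.1% | 21.6% |

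These patterns are not bounds. If one single arm lies three quarters of the way from the lowest arm to T + URT, power with 16 per arm is about 3% (pairs at 0.0056) or 6.5% (0.0167). Equal single arms was the most favourable pattern tried.

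**6. Where the power goes.** The second correction (last two columns) costs 16.8, 12.0, 14.6 and 13.5 points, row by row. The rest of the gap from omnibus power at 0.05 is 24.7, 63.2, 18.0 and 60.9 points, the larger part in every row. That rest combines the move to two contrasts with the unbudgeted 0.017 level. Measured against the nominal 90% instead, the second correction is the larger part in one row only (19 per arm, single arms equal: 14.6 of 26.6 points).

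**7. Is the second correction needed?** With three arms, once the global null is rejected at 0.0167 the remaining hypotheses are single pairs, so unadjusted pairs at 0.0167 form a closed test. Simulated familywise error per outcome was 0.0167 under the global null and 0.0125 to 0.0166 under partial nulls; with the extra Bonferroni it was 0.0138 and about 0.0055. Independently of closure, a claim that needs both contrasts is an intersection-union test and needs no split. Its nominal false-claim rate in the favourable direction is at most 0.0167/2 = 0.0083.

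**8. Unequal variances.** With pooled tests, an SD of 1 in the two equal arms and 0.7 or 0.5 in a distant third arm, the two-sided error for the null pair is 0.029 or 0.038 at the 0.0167 level (0.011 or 0.016 with the extra Bonferroni). If that third arm is a single arm, the false both-arms claim takes half of this, about 0.0145 or 0.019. With unequal-variance tests it stayed at or below 0.009.

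**The case against.** - **The figure 0.0056 is an inference.** This stands. If adjusted pairwise p values were meant to be read at 0.05, each pair is tested at 0.0167 and power is already 29% to 67% with 16 per arm. The text should say which; either way power for the main claim is well below 90%.
- **A reader might infer that the double correction is what leaves power at 17% to 50%.** The figures do not support that: removing it reaches only 29% to 67%.
- **A reader might infer that the double correction is an error, or that dropping it costs nothing.** Neither holds. It is valid and conservative. It also protects single-pair claims when variances differ (step 8), and the plan names Levene's test but no unequal-variance alternative. The closed-test argument does not carry over exactly to Kruskal–Wallis with Dunn tests.
- **TCC vs URT matters too.** The secondary hypothesis concerns the two single arms, so that pair must keep a rule.
- **The primary analysis is by intention to treat.** It takes in all 19 per arm, with imputation, so 22% to 63% is the range if nothing is lost. With single arms equal and 19 per arm, success is more likely than not; it cannot be said that a null result is likely in every case where the hypothesis is true.
- **The Discussion sentence is a conditional remark, not an analysis rule.** True, but it still gives a null result a meaning that this power cannot support.

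**Conclusion.** The point holds. The sample size covers the omnibus test at 0.05 and not the two contrasts that decide the main hypothesis. On the natural joint reading of the Statistical analysis section, power to beat both arms is about 17% to 50% with 16 per arm and 22% to 63% with 19. This rests on f = 0.55 for extensor torque, equal variances and two assumed patterns of means; no effect size is given for flexor torque or H/Q. The second correction accounts for about 12 to 17 points and is unnecessary for the both-arms claim. Most of the shortfall is a matter of sizing and remains after it is dropped: 80% power would take about 20 (single arms equal) to 48 (equally spaced) evaluable per arm with pairs at 0.0167, against 25 to 59 with both corrections.

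**What to change.** **Statistical analysis.** State the pairwise threshold. For each primary outcome analysed by ANOVA, after a significant omnibus test at 0.017, test T + URT vs TCC and T + URT vs URT each at 0.017, with an unequal-variance test if variances differ. Claim superiority to either alone only if both favour T + URT. Keep the Bonferroni adjustment for TCC vs URT, for single-pair claims when variances differ, and for the Kruskal–Wallis/Dunn branch.

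**Sample size.** Beside the omnibus power, report power for the two contrasts at the thresholds actually used, with the assumed means. Under the patterns above this is about 29% to 67% with 16 per arm and 35% to 78% with 19.

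**Discussion.** Say that a non-significant contrast is inconclusive unless its confidence interval excludes a worthwhile difference named in advance, instead of attaching a mechanism to it. Give the confidence level; 98.3% (1 − 0.017) matches the test.

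**Cost.** Wording only, with no extra participants. The stated power for the main claim becomes less favourable, and single-pair claims need the safeguard above.
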